### Study procedures and interventions

2.8

This study will be divided into three periods: a screening period, a treatment period and a follow-up period. The flow chart of this trial is presented in Figure 1.

**Figure 1 fig1:**
[figure not shown]
Flow chart of patients.

#### Screening period: admission to the hospital to the start of surgery

2.8.1

After admission, the patients will undergo an examination and sign an informed consent form after screening. Patients will be instructed on the use of the NRS and CRBD evaluating prior to surgery to avoid confusion.

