However, CRBD is difficult to prevent and treat. The main methods for preventing and treating CRBD include local anesthesia, psychological intervention and drug intervention. Currently, several methods have been proven to be effective for preventing CRBD, such as nerve block, transcutaneous electrical nerve stimulation, lidocaine, intravesical bupivacaine, magnesium sulfate, and nefopam (5–10). Because these methods are primarily implemented intraoperatively, the cost of the procedure increases. Thus, considering the substantial number of patients with indwelling catheters after surgery under general anesthesia, a cost-effective, feasible and effective strategy for preventing postoperative CRBD is needed. Traditional Chinese medicine (TCM) hot compresses have been used for more than 2,000 years. They can dilate local capillaries, improve blood circulation, reduce inflammation and swelling, dispel cold and dampness, alleviate pain and eliminate fatigue. TCM hot compresses offer a technically simple and cost-effective alternative (11, 12). TCM hot compresses can relieve pain and discomfort caused by muscle spasms as well as relieve breast tenderness and pain, post-stroke shoulder-hand syndrome and postpartum urinary retention (12–14). The improved Xiao-Xu-Ming-Tang powder is mixed with coarse sea salt (40–45 °C hot compress) to increase the skin permeability of the active components—the mild heat can dilate the suprapubic capillaries and open the skin stratum corneum pores, and the active compounds (volatile oils, alkaloids) of the medicinal materials are small molecular weight substances that can quickly penetrate the skin, enter the local subcutaneous tissue and bladder meridian, and exert anti-spasm and pain-relieving effects without systemic absorption (no systemic side effects) (15). [name], a renowned TCM expert in Shanghai, and his research team confirmed that Xiao-Xu-Ming-Tang can significantly alleviate catheter-induced bladder discomfort and irritation, as well as pain associated with urinary calculi (16). Based on clinical practice, our hospital’s TCM department optimized the original Xiao-Xu-Ming-Tang formula to form the improved version, which consists of *Notopterygii Rhizoma et Radix* (Qianghuo), *Chuanxiong Rhizoma* (Chuanxiong), *Scutellariae Radix* (Huangqin), *Ephedrae Herba* (Mahuang), *Aucklandiae Radix* (Muxiang), *Aconiti Radix Praeparata* (Zhi Fuzi), *Stephaniae Tetrandrae Radix* (Fangji), *Saposhnikoviae Radix* (Fangfeng), *Amomi Fructus* (Yangchun Sha), and *Paeoniae Radix Alba* (Sheng Baishao). The active components of these herbs have clear pharmacological effects on CRBD: *Notopterygii Rhizoma et Radix* contains volatile oils (e.g., ligustilide) and sesquiterpenoids that dilate local blood vessels and promote transdermal absorption, with its volatile components regulating the bladder meridian and relieving smooth muscle spasm; *Chuanxiong Rhizoma*, *Scutellariae Radix*, and *Ephedrae Herba* contain ephedrine (alkaloid) and volatile oils that inhibit M-cholinergic receptors of bladder smooth muscle and reduce involuntary contractions—the core pathological mechanism of CRBD—and their alkaloid components have good transdermal permeability, exerting local effects through the suprapubic skin; *Aucklandiae Radix* contains volatile oils (e.g., costunolide) for regulating qi and relieving spasm, with volatile components quickly penetrating the skin to act on local bladder meridians; *Amomi Fructus* contains volatile oils that soothe the bladder and relieve micturition urgency, with active components having high transdermal bioavailability on the lower abdominal skin. Most of these medicinal materials have a strong aromatic odor and good transdermal absorption properties; ground into powder and applied externally, they can regulate Zang-Fu organs and meridians to achieve the balance of yin and yang, which has been verified by relevant studies (17). CRBD falls under the categories of stranguria with urgency and abdominal pain in TCM, with its core pathogenesis being qi stagnation and meridian obstruction. Surgical trauma and catheter stimulation give rise to qi stagnation in the bladder meridian, which further induces bladder smooth muscle spasm. The modified Xiao-Xu-Ming-Tang is formulated based on the TCM therapeutic principles of regulating qi, unblocking meridians, and relieving spasm. The selected medicinal herbs target the bladder meridian in the lower abdomen, which accords with the standard TCM clinical practice of syndrome differentiation and treatment.

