#### Primary outcomes

2.2.1

The primary outcomes will be the incidences of moderate and severe CRBD (grades 3 and 4) at 30 min after surgery.

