#### Secondary outcomes

2.2.2

The five secondary outcomes are as follows: (1) the incidence of moderate-to-severe CRBD at 1 h, 6 h, and 24 h after surgery; (2) the NRS score, which is used to evaluate postoperative pain, at 30 min, 1 h, 6 h, and 24 h after surgery, with scores ranging from 0, indicating no pain, to 10, indicating the worst pain imaginable; (3) the incidence of skin discomfort above the pubic symphysis (scald, redness, pruritus, allergy, etc.); (4) vital signs (blood pressure, heart rate, and oxygen saturation) at 10, 20, 30, 40, 50 min, 1 h, 6 h, and 24 h after surgery; and (5) patient satisfaction [24 h after surgery, patient satisfaction using a 5-point scale, with items graded 1 (“very dissatisfied”) to 5 (“very satisfied”)].

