### Sample size

2.6

The calculated sample size for this study is 90 patients: 45 patients in the experimental group and 45 patients in the control group. This is a randomized controlled study in which the experimental group will be treated with a TCM hot compress and the control group will be treated with a sea salt hot compress (a hot compress of a improved Xiao-Xu-Ming-Tang and salt mixture, making the two groups indistinct in smell) The primary outcomes will be the incidences of moderate and severe CRBD in patients with indwelling catheters after transurethral laser lithotripsy. According to previous studies, the incidence of moderate-to-severe CRBD after transurethral laser lithotripsy is 55–87% (3, 9, 20), with an average of approximately 70%. Assuming that the improved Xiao-Xu-Ming-Tang hot compress can reduce the incidence of CRBD by 50%, that is, the incidence of CRBD in the control group and the experimental group are 70 and 35%, respectively. Considering an *α* = 0.05 (two-tailed), a 1 − *β* = 0.9, and a 1:1 ratio, 42 patients are needed for the control group and 42 are needed for the experimental group. However, considering a loss to follow-up rate of 5%, approximately 45 patients will be included in each group.

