### Data management and statistical analysis

2.7

All the statistical analyses will be performed with SPSS version 27.0 (IBM Corporation, Armonk, NY, United States). The baseline data will include clinical data collected before the first intervention. Normally distributed continuous variables will be expressed as means ± standard deviations (SDs); otherwise, they will be expressed as medians and interquartile ranges (IQRs). Categorical variables will be described as numbers (*n*) and percentages (%). The chi-square test will be used to compare the incidence between the two groups, the t test will be used to compare normally distributed continuous variables, and the nonparametric test will be used for other variables. All hypothesis tests are two-sided, and two-sided *p*-values less than 0.05 represent statistical significance.

TSA 0.9.5.10 beta software will employed to verify study power, with preset parameters including two-sided *α* = 0.05, *β* = 0.1, and an expected RRR of 50%. Using the primary outcome (incidence of moderate–severe CRBD), we will derive the cumulative *Z*-value and establish the monitoring boundary to guard against false positives and false negatives induced by multiple testing.

For NNT reporting, we calculate and report the NNT (95% CI) for the primary endpoint (30-min post-surgery moderate–severe CRBD) in the Results section. Defined as 1/ARR, the NNT directly quantifies the clinical impact of the optimized Xiao-Xu-Ming-Tang hot compress, representing the number of subjects needed to prevent one instance of moderate–severe CRBD.

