#### Follow-up period: end of surgery to 24 h after surgery

2.8.3

NRS and RASS scores will be evaluated by a dedicated follow-up researcher at 30 min, 1 h, 6 h, and 24 h after surgery. CRBD grades and patient satisfaction scores will be recorded at the same postoperative time points. The researcher responsible for documentation will complete the CRF. Patients’ vital signs on admission to the PACU, intraoperative anesthetic agents, RASS, NRS, CRBD, and adverse events will be recorded in the electronic data system. The study timeline is presented in Table 1.

**Table 1 tab1:** Timetable of the study period.

Timepoint	Screening period (−2~−1 d)	Preparation period (−1~0 d)	Surgery period (0 d)	Follow-up period (after awakening until 24 h postoperatively)								
		T0		T1	T2	T3	T4	T5	T6	T7	T8	T9
Eligibility screen and informed consent	X											
General condition of the patient^a^	X											
Training^b^		X										
Vital signs^c^	X			X	X	X	X	X		X	X	X
Random allocation		X										
Hot compress												
The CRBD score						X				X	X	X
The NRS score						X				X	X	X
Adverse events record^d^												
Satisfaction of patients												

*T0, Before induction of anesthesia; T1, 10 min after awakening; T2, 20 min after awakening; T3, 30 min after awakening; T4, 40 min after awakening; T5, 50 min after awakening; T6, 1 h after awakening; T7, 6 h after awakening; T8, 12 h after awakening; T9, 24 h after awakening.

a Patients were educated about how to recognize CRBD (for example, suprapubic discomfort or burning with the urge to urinate) and how to distinguish them from surgical pain.

b Obtain the patient’s name, hospitalization number, age, medical history (whether there are the following conditions, serious heart, liver, kidney and other diseases; If the hot compress site has skin injury, ulcer, sensory disturbance, acute closed injury, suppurative infection or acute inflammation and other infectious diseases, skin diseases, severe diabetes, high fever and excessive use of product materials, it is not suitable for hot compress; Patients with prostatic hypertrophy, urethral stricture, and a history of indwelling catheter within 1 year.

c Blood pressure, heart rate, and oxygen saturation.

d Burns, redness, itching, allergies, etc.

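### NRS pain is scored only after surgery and compared without adjustment for centre or a pre-operative score; the comparison is unbiased but may be less precise than it could cheaply be

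*Protocol article*

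**What the plan says.** Section 2.2.2 lists as its second secondary outcome "the NRS score, which is used to evaluate postoperative pain, at 30 min, 1 h, 6 h, and 24 h after surgery". Section 2.8.3 repeats the schedule: "NRS and RASS scores will be evaluated by a dedicated follow-up researcher at 30 min, 1 h, 6 h, and 24 h after surgery". In Table 1 the NRS row has no mark at screening or at T0, whereas vital signs do have a screening value.

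Patients nevertheless meet the scale before surgery. Section 2.8.1 reads: "Patients will be instructed on the use of the NRS and CRBD evaluating prior to surgery to avoid confusion". Table 1 puts training in the preparation period (-1 to 0 days), the same column as random allocation.

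For the analysis, section 2.7 says that "the t test will be used to compare normally distributed continuous variables, and the nonparametric test will be used for other variables". No covariate is named. On baseline data it says only: "The baseline data will include clinical data collected before the first intervention". Section 2.4 stratifies randomization by centre, with 15 patients per arm at each of three centres.

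**The concern.** A post-operative score reflects the treatment, the operation and the catheter, and also how much pain each patient tends to report. If part of that last component shows in a score taken before treatment, a model that includes the score removes it from the error term. The plan teaches the scale before surgery but records no rating, and its named tests could not use one anyway.

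The same tests ignore centre. Because allocation is balanced within centres, centre differences cancel from the treatment difference, yet they stay in the unadjusted standard error.

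What is at stake is the width of the confidence intervals for NRS. The sample size was set for the binary CRBD outcome, and no power is stated for NRS.

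**Working it through.** **The plan's own figure.** Section 2.2.1 defines the primary outcome: "The primary outcomes will be the incidences of moderate and severe CRBD (grades 3 and 4) at 30 min after surgery". Section 2.6 assumes that "the incidence of CRBD in the control group and the experimental group are 70 and 35%, respectively", with two-sided alpha 0.05 and power 0.90. With pooled variance,

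n = [1.96·√(2·0.525·0.475) + 1.2816·√(0.70·0.30 + 0.35·0.65)]² / 0.35² = (1.384 + 0.848)² / 0.1225 = 40.7, so 41 per arm.

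The stated figure is 42, so it reproduces to within one patient. Allowing for 5% loss, 42/0.95 = 44.2, so 45 per arm. None of this depends on NRS.

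**Inputs for NRS.**
- From section 2.6: 42 evaluable patients per arm.
- Assumed, because the document gives none of them: rho from 0.1 to 0.5, SD 1.7, true difference 1 point, and equal SDs before and after surgery.

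**Formulas.**
- Unadjusted standard error: 1.7·√(2/42) = 0.371.
- ANCOVA variance factor: 1 − rho². The confidence-interval width is multiplied by its square root.
- Equivalent n per arm: 42/(1 − rho²).
- Power: Φ(1/(0.371·√(1 − rho²)) − 1.96). Unadjusted, this is Φ(2.696 − 1.96) = Φ(0.736) = 0.77.
- Variance of a change score relative to the post-operative score alone: 2(1 − rho).

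| Assumed rho | Variance factor | CI width factor | Equivalent n per arm | Power | Change-score variance |
|---|---|---|---|---|---|
| no covariate | 1.00 | 1.00 | 42 | 77% | – |
| 0.1 | 0.99 | 0.995 | 42.4 | 77% | 1.8 |
| 0.2 | 0.96 | 0.98 | 43.8 | 79% | 1.6 |
| 0.3 | 0.91 | 0.95 | 46.2 | 81% | 1.4 |
| 0.5 | 0.75 | 0.87 | 56.0 | 88% | 1.0 |

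**Cost of the covariate.** At N = 84 one covariate inflates the variance by roughly 1 + 1/79 = 1.013. At rho 0.1 the net factor is 0.99 × 1.013 = 1.003, so there is no gain. At rho 0.2, 0.3 and 0.5 it is 0.97, 0.92 and 0.76.

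**Other effect size.** For an assumed difference of 0.5 SD, power goes from 63% unadjusted to 63%, 65%, 67% and 75% at the same four values of rho.

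**Chance imbalance.** The standard error of a baseline difference is √(2/42) = 0.218 SD. A difference of that size moves the post-operative comparison by rho times as much: 0.3 × 0.218 = 0.065 SD, or 0.5 × 0.218 = 0.109 SD. The unadjusted standard error already allows for this.

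**Centre.** The document gives no between-centre variation in NRS, so the gain from adjusting for centre cannot be sized. Three centres cost two degrees of freedom.

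**The case against.** The strongest reply is that nothing here is wrong. NRS is a secondary outcome meant to measure pain after surgery, and a randomized comparison of post-operative scores is valid. Covariates for secondary outcomes are often left to an analysis plan, and this article condenses a fuller protocol. All of that stands, and it limits the point to efficiency. But the article does fix both the NRS schedule and the test, so a comment on those choices is fair.

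A reader might infer that these patients are known to differ in pain before treatment because the Introduction mentions "pain associated with urinary calculi". That phrase describes what another team reported the original formula to relieve. It does not describe pre-operative pain in this sample, and the document gives no level or spread for it. The operation treats the stone and a new catheter is then placed, so a weak correlation is quite plausible, and it may differ between 30 min and 24 h.

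A reader might also infer that chance baseline imbalance biases the NRS results or carries over in full. It does neither: it carries over only in proportion to the regression slope, and the type I error rate is not inflated.

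The timing objection also has force. Section 2.1 gives a study period of November 2024 to November 2025, the article appeared in April 2026, and the abstract speaks of inclusion in the past tense. If enrolment is over, a pre-operative score can no longer be collected. Adjustment for centre remains possible.

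**Conclusion.** The point holds as a low-severity suggestion. The plan schedules no pre-operative NRS score and names an unadjusted test despite stratifying by centre, so some precision on a secondary outcome may be lost. The size is uncertain: about 1% to 25% of the variance for rho of 0.1 to 0.5, negligible up to about 0.2 and material only towards 0.5. The power figures also rest on the assumed SD and difference.

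The document does not support a claim that a worthwhile gain is certain, or that one extra question would secure it. The planned t or nonparametric test would not use the score, so the analysis must change too. The primary outcome, its sample size and the validity of the NRS comparison are untouched.

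**What to change.** 1. In section 2.7, compare NRS at each time point with a linear model (ANCOVA) adjusted for centre, or a rank-based version if the scores are clearly non-normal. This needs no new data and can be done even if enrolment has closed.
2. Where enrolment still allows, have each patient rate current pain as the practice item at the training contact and record it. Specify that this comes before random allocation, since Table 1 places both in one column. Mark it in the NRS row of Table 1.
3. Add that score as a covariate in the same model. Do not use change scores: with equal SDs they are less precise than the post-operative score alone whenever rho is below 0.5.
4. When section 2.7 is edited, check the NRS times. The text gives 30 min, 1 h, 6 h and 24 h, while the NRS marks in Table 1, as the extracted text shows them, fall at T3, T7, T8 and T9 (30 min, 6 h, 12 h and 24 h). This may be an artefact of extraction.

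The cost is one case report form field, a few seconds per patient, a possible missing baseline value, and three model degrees of freedom (two for centre, one for the score). N = 90 and the primary analysis stay as they are.

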#### Treatment period: start of surgery to 1 h after the end of surgery

2.8.2

Anesthesia protocol (all procedures will be performed under standardized anesthesia): Patients will be admitted to the operating room without pre-anesthesia medication and undergo electrocardiogram (ECG), pulse oxygen saturation (SpO_2_), blood pressure, and depth of anesthesia (BIS or Narcotrend) monitoring. Five hundred milliliters of Ringer’s solution will be given through peripheral venous access. Sufentanil (0.1–0.3 μg/kg) and cyclopofol (0.4–0.6 mg/kg) will be used for the induction of general anesthesia. A muscle relaxant (rocuronium 0.6 mg/kg) will be given, and a laryngeal mask will be placed when the depth of anesthesia is deemed adequate (a BIS of 45–60). After anesthesia induction, a hot compress will be placed over the patient’s pubic symphysis immediately by a research nurse (to avoid a burn injury, the temperature of the hot compress should remain between 40 and 45 °C during continuous monitoring at the contact surface with a temperature probe. The surgery will be performed as usual. The injection rates of propofol and remifentanil will be adjusted according to depth of anesthesia and the patient’s hemodynamics during the operation, and the depth of anesthesia must be maintained at 45–60. The volumetric ventilation mode will be adopted with a tidal volume set at 6–8 mL/kg, an airway pressure maintained at 30 cmH_2_O, and the ETCO_2_ maintained at 35–45 mmHg. The patient’s ECG, HR, BP, RR, SpO_2_ and EtCO_2_ will be monitored intraoperatively. At the end of surgery, the anesthesiologist will discontinue infusion of all anesthetics and then administer sugammadex (2 mg/kg). A no. 18 indwelling catheter will be placed by the urologist, and a balloon will be expanded with 10 mL of distilled water. The laryngeal mask will be removed when the patient can open his/her eyes when prompted, and he/she will be transferred to the postoperative recovery room (PACU) for observation for at least 60 min before being transferred back to the ward. All cases of moderate or severe CRBD during resuscitation will be managed and recorded by the resuscitation room physician.

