
Our modification is dual-oriented: to adapt the formula for transdermal hot compress application and to achieve targeted relief of CRBD symptoms. (1) Component optimization: Based on the original prescription, Yangchun Sha and sheng Baishao were added to strengthen the actions of regulating qi, relieving spasm, and unblocking the bladder meridian, thereby exerting a targeted effect on CRBD caused by bladder smooth muscle spasm. Meanwhile, the dosages of Máhuáng and Fángjí were adjusted to reduce excessive pungency and ensure transdermal safety. (2) Formulation transformation: The original water decoction was converted into a powder mixture with coarse sea salt. The powder form increases the specific surface area of the medicinal materials, facilitating transdermal absorption. Coarse sea salt acts as a heat storage medium to maintain a stable temperature (40–45 °C) for hot compression, which is the key modification for adapting the prescription to transdermal hot compress application. (3) Efficacy re-orientation: The modified prescription abandons the systemic regulatory effect of oral administration and instead emphasizes local meridian regulation and transdermal delivery over the suprapubic region. It aims to directly alleviate bladder discomfort via the skin and meridians, which better matches the clinical demand for perioperative local intervention in CRBD.

Therefore, we hypothesized that improved traditional Chinese medicine hot compresses could reduce the incidence of moderate-to-severe CRBD in patients, providing a new method for preventing CRBD.

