### Randomization and masking

2.4

An envelope lottery will be used to randomize patients into groups, and because the study will be conducted across 3 centers, stratified randomization is required, with 30 patients included from each center, 15 of whom will be assigned to the experimental group and the remaining 15 will be included in the control group. The study will be conducted in double-blinded manner, and patients were only informed that they were enrolled in a clinical trial for the prevention of postoperative CRBD and were assigned to a study group with a unique study number, and the specific grouping (experimental/control) and the differences in the composition of the hot compress bags (full dose/one-tenth dose of medicinal powder) were not disclosed to the patients at any stage before, during, or after the surgery. The hot compress will be placed over the patient’s pubic symphysis immediately after intubation under general anesthesia and removed 60 min after surgery by a site nurse who will not be involved in follow-up visits. Patients, anesthesiologists, surgeons, note-takers, data registrars and analysts will be unaware of the group assignments. The TCM package will be distributed to each center by the Department of TCM of Shanghai Fourth People’s Hospital. Both groups will emit the smell of TCM, which are indistinguishable by odor alone. Group assignments will be maintained by the personnel at the main site who are not involved in the study but rather responsible for the study group numbers and hot compresses. Only when the patient has a serious adverse reaction that is suspected to be related to the intervention itself will he or she be responsible for the emergency unblinding of the patient to ensure timely treatment of the condition.

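### A case of moderate or severe CRBD that is treated and settles before the 30-minute grade counts as event-free, yet the NNT is to be read as cases prevented

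*Protocol article*

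**What the plan says.** The Introduction hypothesises that the compress "could reduce the incidence of moderate-to-severe CRBD in patients, providing a new method for preventing CRBD". Section 2.2.1 turns this into status at one time: "The primary outcomes will be the incidences of moderate and severe CRBD (grades 3 and 4) at 30 min after surgery". Section 2.8.3 has CRBD graded at the scheduled postoperative assessments, the first at 30 minutes: "CRBD grades and patient satisfaction scores will be recorded at the same postoperative time points". No earlier grade is scheduled, and section 2.2.2 lists no outcome for treatment of CRBD.

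Section 2.8.2 sends patients to the recovery room "for observation for at least 60 min before being transferred back to the ward" and adds: "All cases of moderate or severe CRBD during resuscitation will be managed and recorded by the resuscitation room physician". It gives no trigger, drug or timing, and no link to the 30-minute grade.

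Section 2.7 compares incidences by chi-square test and promises: "we calculate and report the NNT (95% CI) for the primary endpoint (30-min post-surgery" and so on. It then interprets that NNT as the number of patients needed to prevent one case of moderate or severe CRBD.

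**The concern.** The recovery stay spans the 30-minute grading, so the condition that defines the endpoint can be treated before the endpoint is read. A patient who is grade 3 or 4 at 15 minutes, is treated, and is grade 1 or 2 at 30 minutes counts as a success. That patient had the condition; it was not prevented.

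The endpoint definition, the management rule and the interpretation of the NNT are all fixed in this article, and the third does not follow from the first two. Prevention is the trial's central claim. Unless early-managed cases are shown by arm, readers cannot separate CRBD that the compress prevented from CRBD that occurred and was treated.

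**Working it through.** **Inputs from section 2.6.** Control rate 70%, active rate 35%, two-sided alpha 0.05, power 0.90, 1:1 allocation, 42 per arm, 45 per arm after 5% loss.

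**The plan's own figure.** The pooled normal formula for two proportions gives 41 per arm, close to the stated 42. Then 42/0.95 = 44.2, rounded up to 45. The sample size is not in dispute.

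**Assumption.** Let f be the share of moderate or severe cases treated and settled before the 30-minute grade. The article gives no value, so f is varied. Power below is exact, by full enumeration of the uncorrected chi-square test at 45 per arm, unless stated otherwise.

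**Case A: 70% and 35% are rates without early treatment; f is equal in both arms.** Control rate at 30 minutes = 0.70(1−f); active rate = 0.35(1−f); NNT = 1/(difference).

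| f | Control | Active | Risk ratio | NNT | Power |
|---|---|---|---|---|---|
| 0 | 70% | 35% | 0.50 | 2.9 | 0.92 |
| 5% | 66.5% | 33.3% | 0.50 | 3.0 | 0.89 |
| 10% | 63% | 31.5% | 0.50 | 3.2 | 0.85 |
| 20% | 56% | 28% | 0.50 | 3.6 | 0.77 |

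At f = 20%, 45 × 0.70 × 0.20 = 6.3 control patients and 45 × 0.35 × 0.20 = 3.15 active patients had the condition but count as event-free.

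**Case B: 70% and 35% already reflect early treatment; f is equal in both arms.** Power (0.92) and the 30-minute NNT (2.9) do not change. The rates of moderate or severe CRBD either at 30 minutes or treated and settled earlier are 0.70/(1−f) and 0.35/(1−f):

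| f | Control | Active | NNT |
|---|---|---|---|
| 5% | 73.7% | 36.8% | 2.7 |
| 10% | 77.8% | 38.9% | 2.6 |
| 20% | 87.5% | 43.8% | 2.3 |

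**Unequal settling, on the Case A footing** (power here by normal approximation at 42 per arm, where f = 0 gives 0.91):

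- Control 10%, active 30%: 0.70 × 0.90 = 63% against 0.35 × 0.70 = 24.5%. Risk ratio 0.245/0.63 = 0.39; power 0.96.
- Control 30%, active 10%: 0.70 × 0.70 = 49% against 0.35 × 0.90 = 31.5%. Risk ratio 0.315/0.49 = 0.64; power 0.37.

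The direction therefore depends on where more cases settle. One reclassified patient moves an arm's rate by 1/45 = 2.2 percentage points.

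**The case against.** Status at 30 minutes under usual care is a coherent endpoint. The article fixes it consistently and names the 30-minute endpoint when it introduces the NNT. Counting a treated, settled patient as a non-event is a legitimate treatment-policy choice. Supportive analyses and rescue details are often left to an analysis plan or full protocol, which are not shown. Early treatment is also partly inferred: section 2.8.2 does not say that management happens before 30 minutes or works by then. A patient managed early who is still grade 3 or 4 at 30 minutes is already an event.

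Most of this stands. The endpoint need not change, and the absence of a sensitivity analysis would not by itself be a finding. What remains is that section 2.7 states in this article what the NNT means, and that meaning does not follow from a 30-minute status read after open-ended treatment.

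A reader might go further and infer that the primary test is biased in favour of the compress. The documents do not support that. With equal settling the risk ratio is unchanged and the risk difference shrinks or stays as planned, which is conservative. Section 2.4 says: "Patients, anesthesiologists, surgeons, note-takers, data registrars and analysts will be unaware of the group assignments". This makes unequal treatment decisions less likely. It does not settle the matter in the other direction either: the list does not name the recovery-room physician, and blinding does not ensure that equal shares of cases settle if severity differs between arms.

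**Conclusion.** The point holds as a mismatch between endpoint, recovery management and the stated meaning of the NNT. It is not an error in the primary test. That an early-treated, settled case counts as event-free follows from the definitions alone. The size rests wholly on the assumed f, and the article cannot decide between Case A and Case B. For equal shares up to 20%, the risk ratio stays 0.50; the 30-minute NNT is 2.9 to 3.6 in Case A, and in Case B it stays 2.9 while the NNT counting early cases falls to 2.3. For the unequal shares tried, the risk ratio is 0.39 or 0.64. It would be too strong to say that the trial is underpowered or the result inflated: no early-treatment rate, and no difference in it between arms, is documented. This is a minor-to-moderate improvement.

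**What to change.** Keep the 30-minute grade as the primary endpoint and leave patient care unchanged. In section 2.7:

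1. Describe the NNT as cases avoided at 30 minutes under usual recovery care.
2. Report by arm the number of patients managed for moderate or severe CRBD before their 30-minute grade.
3. Pre-specify, before unblinding, one supportive chi-square analysis that counts those patients as events together with those at grade 3 or 4 at 30 minutes, and give its NNT beside the main one.
4. Take the episode time and treatment from the recovery record, and define "before" by the actual time of each patient's grade. The rule then works whether the clock starts at the end of surgery (section 2.2.1) or as in Table 1 ("T3, 30 min after awakening").

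The cost is a short dated addition and a little analysis. The planned study period ended in November 2025; if the data are already unblinded, the analysis must be labelled post hoc. There are drawbacks. The cases are to be recorded, but the article requires neither the episode time nor the treatment type, and section 2.8.3 time-stamps data on entry, which may be later than the episode. Detection by the recovery physician is unscheduled and may include emergence agitation that resembles grade 4 behaviour. For these reasons the analysis should be supportive only.
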